### Qualitative data

#### GP feedback interview

At the end of the intervention delivery phase (i.e. after both the initial and 6-month medication reviews are completed), qualitative interviews will be conducted with up to 10 GPs in the intervention arm practices. GPs will be interviewed as soon as possible after receipt of the training to deliver the PolyPrime intervention and subsequent delivery of the intervention to patients, using a semi-structured interview guide. The interviews will be completed either face-to-face at a location that is mutually convenient for both the GPs and the researcher (e.g. GP practices), via the telephone or video-call. GPs will be given an honorarium of £46/€54 to compensate them for the time associated with participation in an interview. GPs will be asked about their views on the following:
Acceptability of study procedures including patient screening and recruitment and support provided by the research teamExperience of the PolyPrime intervention including how it enhanced knowledge, skills and confidence in abilities
Online video (and supporting materials)Weekly practice meetingsPrompts/cuesPatient recall process—including mode of deliveryAcceptability of the intervention (questions based on TFA) (Table 1) [22].

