#### Mechanisms of action

Data will be collected to identify the intervention’s likely mechanisms of action (i.e. the process whereby an intervention component exerts its effect). Firstly, we will explore if the online video component brought about changes in the GPs’ beliefs about capabilities (e.g. their self-efficacy) [27] to provide appropriate polypharmacy for the effective clinical management of older people in primary care. Secondly, we will explore if the patient recall process was effective in bringing about positive attitudes towards the medication reviews (‘Salience of consequences’ for GPs). Finally, we will explore if weekly meetings (BCT: ‘Action planning’) and practice staff delivering prompts to GPs (BCT: ‘Prompts/cues’) were perceived to be effective and/or useful in reminding GP practices to organise appointments and reminding GPs to deliver a medication review to the patient (see Table 3). In our qualitative assessment of the likely mechanisms of action for the PolyPrime intervention, we will use established methods that link BCTs to theoretically defined mechanisms of action [28]. For example, we can assess the extent to which the BCT ‘prompts/cues’ was perceived to influence memory, attention and decision processes or relevant behavioural cueing processes that help initiate and maintain medication reviews, as part of routine care. This analysis of potential mechanisms of action will help refine the process evaluation and theoretical underpinning of any subsequent full trial of future iterations of the PolyPrime intervention [9]. This will be integrated into the interpretation phase of the framework analyses described below.

**Table 3 Tab3:** Intervention component and data collected as part of process evaluation

Intervention component	Impact	Data collected	Data source^**a**^
Online video	Changes in the GPs’ beliefs about capabilities (e.g. their self-efficacy) to prescribe appropriate polypharmacy during a consultation with an older patient	GP views on the usefulness of the online video	GP feedback interviews
Weekly meetings	Weekly meetings are perceived to be effective in GPs making plans to schedule patient appointments	The number of weekly practice staff meetings held	Data collection forms completed by practice staff
		GP views on the effectiveness/usefulness of weekly meetings	GP feedback interviews
		Practice staff views on the effectiveness/usefulness of weekly meetings	Practice staff feedback interviews

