Prompts/cues	Prompts from practice staff were perceived to be effective in reminding GPs to deliver a medication review to patients	The number of prompts GPs receive from practice staff to conduct medication reviews	Data collection forms completed by practice staff
		GP views on the effectiveness/usefulness of receiving prompts	GP feedback interviews
		Practice staff views on the effectiveness/usefulness of delivering prompts	Practice staff feedback interviews
Patient recall	GPs reporting positive attitudes towards the medication review	GP views on the impact of the intervention	GP feedback interviews

*GP* General Practitioner

^a^Based on data collected from the 6 intervention arm GP practices

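### The GP interview topic presumes improvement, although the stated aim is to find out whether capability beliefs changed

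*Protocol article*

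**What the plan says.** The GP feedback interview section says that GPs will be interviewed "using a semi-structured interview guide" and lists the topics on which their views will be sought. The topic on experience of the intervention includes "how it enhanced knowledge, skills and confidence in abilities", and beneath it stand the online video, the weekly meetings, the prompts and the patient recall process. The interview is held at the end of delivery, "after both the initial and 6-month medication reviews are completed", and "qualitative interviews will be conducted with up to 10 GPs in the intervention arm practices".

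The Mechanisms of action section sets out what these interviews are meant to answer. For the video: "we will explore if the online video component brought about changes in the" GPs' beliefs about capabilities, with self-efficacy given as the example. In Table 3, the video row lists as data "GP views on the usefulness of the online video" and as source the GP feedback interviews, with no second source.

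The Practice staff feedback interview section has a parallel topic on experience of the intervention. It carries no clause about enhancement.

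**The concern.** One objective of the process evaluation is to identify likely mechanisms of action. For the video, the hypothesised mechanism is a change in how capable GPs feel of prescribing appropriate polypharmacy. To test that, even qualitatively, the interview must make it as easy for a GP to say that nothing changed, or that confidence fell, as to say that it rose.

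A topic that asks how something was enhanced does not do this. It invites the GP to describe a benefit, and a GP who saw none has to reject the premise before answering. The likely error runs one way, towards support for the mechanism. The section says that this analysis will inform the theoretical basis and process evaluation of any later full trial, so a mechanism that looks supported because of the wording could be carried forward.

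**Working it through.** The plan gives no figure on this point and no arithmetic applies. The check is a comparison of the relevant sections.

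1. **Topic against aim.** The topic asks *how* the intervention *enhanced* three attributes. The aim in Mechanisms of action is to explore *if* the video changed beliefs about capabilities. The aim allows three answers (better, no change, worse); the topic as worded names one. The two do not match.

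2. **GP topic against staff topic.** The two interview sections are built alike: study procedures, experience of the intervention, acceptability. Only the GP version adds the presumption of improvement. Neutral wording was therefore available and is used for the other group.

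3. **Other sources for the capability mechanism.**
   - Table 3, video row: GP feedback interviews only.
   - Video administration page (Table 2): logins and plays, which measure exposure and not belief.
   - Patient questionnaire and staff topic guide: the Intervention acceptability section says that neither contains a self-efficacy question.
   - Audio-recorded reviews: coded for additional behaviour change techniques and emerging themes, not for GPs' beliefs.
   - Timing: the GP interview comes after both reviews, and the article lists no capability measure before the intervention for comparison.

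4. **Whether later steps can correct it.** At least two researchers analyse each transcript independently. That protects against one analyst's reading, but both read answers to the same question. Triangulation compares five data sets. For this theme the other four hold little direct evidence, so the comparisons would mostly be coded as silence or not applicable, and dissonance would rarely arise. Table 4 also gives the number of participants mentioning a theme as an example of prominence, so led answers could make the theme look more prominent.

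5. **What is not shown.** The topic list is a summary. The article reproduces no stem or probe from the guide. Steps 1 to 4 therefore establish a mismatch and a risk that depends on the wording being carried into the guide.

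**The case against.** The strongest reply is that a topic heading is not a question. Interviewers with a semi-structured guide can ask openly and follow up on negative remarks, and the stated aim is open. This stands as a limit: the documents do not show that any GP will be asked a leading question. It does not remove the point, because the heading is what the article says GPs will be asked about.

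A second reply is that the interview has other routes to negative views. Items framed on the theoretical framework of acceptability cover self-efficacy, perceived effectiveness, burden and opportunity costs for GPs; there is a yes/no acceptability question; and the coding has an inductive phase. This also stands in part. A reader might infer that the interview could never count against the mechanism, and these items show that this goes too far. They are not a full substitute, however. Table 1 defines self-efficacy as confidence to do what taking part requires, whereas the mechanism in Table 3 concerns capability to prescribe appropriate polypharmacy.

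Three further inferences are tempting and not supported:

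- **Table 3 has the same fault in its patient recall row**, which gives the impact as "GPs reporting positive attitudes towards the medication review". That column states the hypothesised effect. The text asks openly ("we will explore if the patient recall process was effective in bringing about positive attitudes towards the medication reviews"), and the data cell beside it is neutral. No change is needed there.
- **The bias can be expressed as a percentage of GPs.** No share of GPs reporting enhanced confidence is planned. The interviews go to framework analysis, so such a figure would describe a quantity that the plan does not define.
- **The honorarium encourages agreeable answers.** The article describes it as compensation for time, and nothing links it to the content of answers.

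**Conclusion.** The point holds as a wording fault with a specific consequence. The GP topic presumes improvement, contrary to the article's own open question, and it bears on the only source that Table 3 lists for the capability mechanism. If the topic is asked as written, the risk is a bias towards a positive finding that independent coding and triangulation cannot remove.

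Its size cannot be quantified from the documents. It is confined to GP self-report on knowledge, skills and confidence, in at most 10 interviews.

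The conclusion rests on two assumptions: that the guide follows the topic as printed, and that Table 3 is a complete list of sources for this mechanism. If the guide already uses neutral stems, only the printed description needs correcting.

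**What to change.** Reword the topic to: *whether, and if so how, it changed (improved, did not change or worsened) knowledge, skills and confidence in abilities*. Make sure that the interview guide uses neutral stems for each component, with a standard probe for no change and for negative effects. In the analysis, describe the findings on this theme by direction, including GPs who reported no change or a worsening.

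The cost is a minor revision of the topic guide. It may need ethics committee review, since the Data management and monitoring section says that protocol modifications are submitted to the committees. The article does not say how many GP interviews have been held. For any already done, report the wording that was used and interpret positive answers on this theme in that light.

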#### Practice staff feedback interview

At the end of the intervention delivery phase (i.e. after both the initial and 6-month medication reviews are completed), an interview will be conducted with one member of practice staff (i.e. practice manager or receptionist) from each intervention arm practice (i.e. those involved in implementing the intervention within the practice). Practice staff will be interviewed via telephone as soon as possible after medication reviews have been completed with all recruited patients, using a semi-structured interview guide, at a time convenient to them. Practice staff will be asked about their views on the following:
Acceptability of study procedures including patient screening and recruitment and support provided by the research teamExperience of the PolyPrime intervention
Weekly practice meetingsScheduling appointmentsPrompts/cuesAcceptability of the intervention (questions based on TFA) (Table 1) [22].

#### Audio-recorded medication reviews

As outlined above (see GP and patient recruitment section), GPs and patients will be asked to consent to having the medication review discussions audio-recorded. Due to the current coronavirus restrictions in place, these medication reviews will be conducted either face-to-face, via the telephone or video-call. If possible, each recruited GP from the intervention arm practices will be asked to audio-record one patient’s initial and 6-month follow-up medication review appointments. The GPs will be reminded by a member of the research team to undertake this activity for one of their recruited patients. Audio-recording equipment will be provided by the research team.

### Quantitative analysis

Analysis in relation to study-specific data collection forms and patient questionnaires will use descriptive statistics (e.g. counts, means, standard deviations) and will be conducted using SPSS (version 26.0). Recorded practice-level data will relate to the number of times the intervention GPs access the online video, the number of weekly practice staff meetings held at which explicit plans are made to recall patients for medication reviews, and the number of prompts GPs receive from practice staff to conduct medication reviews. These counts will provide an indication as to whether the intervention has been delivered and received as intended (i.e. intervention fidelity), in conjunction with the outcome data collected in the pilot trial [14]. Patient-level data will be available from the patient feedback questionnaires (see Additional File 1). The acceptability of the study procedures and medication reviews to patients will be assessed via responses to questions (yes/no), scales (Likert-type) or a series of statements relating to acceptability.

### Qualitative analysis—feedback interviews

Analysis of the post-intervention feedback interviews will use a framework analysis [29, 30], which will involve seven stages. The first stage will involve an in-depth familiarisation process. Coding of the transcripts will then take place in two phases. The second stage (first coding phase) will adopt a deductive approach using the TFA constructs [22] to frame the questions relating to the overall acceptability of the intervention in the GP and practice staff interviews (see the “Intervention acceptability” section and Table 1). The third stage (second coding phase) will adopt an inductive approach, in which emerging themes will be identified. This will be followed by the development of a working analytical framework (Stage 4), applying the analytical framework (Stage 5), charting data into the framework matrix (Stage 6) and interpreting the data (Stage 7). All transcripts will be analysed independently by at least two members of the research team. Two sets of analysis will be undertaken, one for each professional group (i.e. GPs and practice staff).

### Qualitative data analysis—medication review appointments

Analysis of the medication review appointment transcripts will be conducted in a similar way to that outlined above. The second stage (first coding phase) will adopt a deductive approach using the BCT taxonomy [13] which will be used to assess if GPs delivered any additional BCTs during the patient recall process. The third stage (second coding phase) will adopt an inductive approach, in which any additional emerging themes will be identified.

### Triangulation of quantitative and qualitative data

Once all quantitative and qualitative data have been analysed separately by the researchers, the results from all five data sets (GP feedback interviews, practice staff interviews, patient feedback questionnaires, medication review appointment recordings, study-specific data collection forms) will be compared. This will follow a triangulation protocol [31] involving six steps (Table 4). Step 1 will involve two researchers examining the interpretative summaries of all analyses to identify the key findings for each data set. The findings related to each research question (outlined above) from all five data sets will be sorted and separated into three files (one for each research question—fidelity, acceptability, mechanisms of action). Step 2 will involve researchers reviewing the contents of each file to identify the key themes discussed in each data set to create a unified list of themes. These themes will form the rows of a convergence coding matrix used to summarise similarities from the second step; each key finding will be compared across the five data sets to create the matrix. For each key finding, paired comparisons will be made to compare the data coming from each data set. The relationship between data will be marked as one of four categories: silence, dissonance (or disagreement), partial agreement and agreement (see Table 4). Comparisons will be labelled as not applicable to denote the source of data which has supplied a theme or when neither data set in a paired comparison contained data related to the finding. This will be followed by convergence assessment (Step 3) and completeness comparison (Step 4). The level of agreement between the two researchers with respect to the degree of convergence between data sets (in both meaning and prominence of key findings) will then be calculated (Step 5). A method established by Miles and Huberman will be used, whereby agreements are scored with 1 and disagreements scored with 0, and the percentage agreement calculated [32]. Miles and Huberman suggest that an inter-coder reliability of 80% agreement on level of convergence is acceptable agreement among multiple coders. Any disagreements will be resolved by consensus through discussion with another researcher. The triangulated results will then be presented to the wider research team for discussion and to make a final decision on the interpretation of the findings (Step 6). All process evaluation activities have been summarised in Table 5.

**Table 4 Tab4:** Triangulation protocol

Step	Activity
1. Sorting	Sort findings from each data set to identify the key findings that address each research question of interest to determine areas of content overlap and divergence. A list of the key themes will be compiled and added to the convergence coding matrix
2. Convergence coding	Compare the findings to determine the degree of convergence of (a) essence of the meaning and prominence (e.g. the number of participants mentioning a theme) of the themes presented and (b) specific examples provided in relation to each theme. Characterise the degree and type of convergence using the following concurrence coding scheme within theme areas:
Convergence coding scheme	
Agreement	There is full agreement between the sets of results on both elements of comparison (e.g. meaning and prominence are the same and specific examples provided are the same)
Partial agreement	There is agreement on one but not both components (e.g. the meaning or prominence of themes is the same or specific examples provided are the same)
Silence	One set of results covers the theme or example, whereas the other set of results is silent on the theme or example
Dissonance	There is disagreement between the sets of results on both elements of comparison (e.g. meaning and prominence are different and specific examples provided are different)
3. Convergence assessment	Review convergence coding matrix to provide a global assessment of the level of convergence. Document when and where researchers have different perspectives on convergence or dissonance of findings
4. Completeness comparison	Compare the findings from the convergence coding matrix to create an overarching summary of the findings, highlighting both unique and similar contributions to each research question
5. Researcher comparison	Determine the degree of agreement among researchers on triangulated findings. Any disagreements will be resolved by consensus through discussion with another researcher
6. Feedback	Feedback of triangulated results to the wider research team for review and clarification

Adapted from [31]

**Table 5 Tab5:** Process evaluation overview

Activity	Data collection	Participants	Timepoint	Duration	Analysis
Online video access	No. of times logged in dates, no. of times pressed play	GPs^a^	Before medication reviews 1 and 2^b^	n/a	Counts
Weekly practice meetings	No. of meetings	Practice staff^a^	Before medication reviews 1 and 2^b^	n/a	Counts
Medication review appointments	No. of appointments scheduled and attended	Practice staff^a^	Before and medication reviews 1 and 2^b^	n/a	Counts and reasons for non-attendance
Prompts	No. of prompts GPs receive from practice staff to conduct medication reviews	GPs and practice staff^a^	Before and medication reviews 1 and 2^b^	n/a	Counts
Medication review	Audio-recording	GPs^a^	Medication reviews 1 and 2^b^	10-30 mins	Thematic analysis; BCT coding
GP feedback	Semi-structured interview	GPs^a^ (one per practice)	After medication review 2	Up to 45 mins	Thematic analysis
Practice staff feedback	Semi-structured interview	Practice staff^a^ (one per practice)	After medication review 2	Up to 30 mins	Thematic analysis
Patient feedback	Questionnaire	Patients^a^ (all)	After 9-month follow-up questionnaires completed	10-15 mins	Quantitative and qualitative

^a^From intervention arm practices

^b^Initial medication review (1) and six-month follow-up medication review (2)

### Data management and monitoring

All participants (patients, GPs, practice staff and GP practices) will be given a unique study ID number and data will be anonymised/pseudonymised (e.g. study-specific data collection forms and interview transcripts). Personal data including consent forms, completed questionnaires or transcripts will be held in a locked filing cabinet, within a locked office on a secure keycode-protected floor of the School of Pharmacy, Queen’s University Belfast (QUB) or the School of Pharmacy and Pharmaceutical Sciences, TCD. Electronic data will be stored within the QUB or TCD network space and will be password-protected to ensure confidentiality. Interviews will be digitally recorded (with permission and written, informed consent), transcribed and checked for accuracy. Once transcripts have been checked for accuracy recordings will be deleted and transcriptions stored within QUB or TCD. All participant consent forms, questionnaires, study-specific data collection forms and transcripts stored at TCD will be transferred to QUB, in line with General Data Protection Regulation guidelines for transferral of data, upon study completion. This will be done via recorded delivery for hard copy data and encrypted email for electronic data. When the study has been completed, the forms and transcripts will be securely stored for 5 years and then destroyed. The investigators will conduct the study in compliance with the protocol given approval/favourable opinion by the relevant RECs. Changes to the protocol may require REC approval prior to implementation, except when modification is needed to eliminate an immediate hazard(s) to patients. The CI and trial team, in collaboration with the sponsor, will submit all protocol modifications to the RECs for review in accordance with the governing regulations. Protocol compliance will be monitored by the trial team who will undertake site visits or telephone calls (if pandemic restrictions are in place) to ensure that the trial protocol is adhered to, such as, scheduling of medication reviews, contacting patients for appointments). Study paperwork will be reviewed, such as questionnaires and consent forms, to ensure that they are being completed appropriately and fully. An independent Trial Steering Committee has been established (consisting of two academic GPs, a health services researcher and statistician) which is overseeing the conduct of the trial and advising on safety in respect of the study.

The findings of this process evaluation will be communicated to all participants, published in relevant journals and presented at conferences. In addition to publishing scientific papers, we also plan to host a seminar for participating practices and patients in convenient locations to present the findings to them. This will be contingent on any pandemic restrictions that may be in place at that time.

